## AE Reporting

Expected Aes will be reported to the JHM IRB and reviewed at the time of the annual review. The University of Wisconsin team will enter all expected adverse events into the REDCap database within 2 weeks. The JHU team will compile all Adverse Events from both institutions for the annual review by the JHM IRB. Any drug-related SAEs or multiple occurrences of an AE determined to be an unanticipated problem will be reported by both institutions to the Johns Hopkins Institutional Review Board and the Johns Hopkins Cancer Center Clinical Research Committee. Drug-related SAE’s will be reported to all regulatory agencies by the study PI ([name]) within 7 working days. Any drug-related SAEs reported by a study participant at the University of Wisconsin will be reported to the JHU PI within 3 business days, in order to allow sufficient time for the expedited reporting by the JHU PI. Unanticipated or unexpected AE is defined as any AE not listed in available sources including the labeling, the Investigator’s Brochure, or this protocol.

PHARMACEUTICAL INFORMATION

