# ADVERSE EVENTS: LIST AND REPORTING REQUIREMENTS

Because this is a pilot study evaluating tolerability of a new intra-anal treatment, the stopping rule for safety is the presence of drug-related Grade 3 toxicity in any organ system (including gastrointestinal, dermatologic, and neurologic toxicities) delineated in CTCAEv4.0. In the event of two identical unexpected treatment-related Grade 2 or greater toxicities in any organ system ( or other Grade 3 or greater toxicities), accrual will be suspended pending further review.

Subjects who become pregnant during study will be required to discontinue drug. Although not considered an adverse event, pregnancy will be reported in the same way. Whenever possible, a pregnancy should be followed to term, and the status of mother and child reported. The Pregnancy Notification form will be sent to the principal investigator ([name]) within 48 hours of discovery. Whenever possible, the Follow-up Pregnancy Outcome Form will be filled after delivery.

Finally, if there is evidence of disease progression at the interval visit regardless whether the progression may or may not be associated with Artesunate, patients will undergo HRA biopsy and ablation at that point.

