| **FDA REPORTING REQUIREMENTS FOR SERIOUS ADVERSE EVENTS (21 CFR Part 312)**  **NOTE:** Investigators **MUST** immediately report to the sponsor (NCI) **ANY** Serious Adverse Events, whether or not they are considered related to the investigational agent(s)/intervention (21 CFR 312.64)  An adverse event is considered serious if it results in **ANY** of the following outcomes:   1. Death 2. A life-threatening adverse event 3. An adverse event that results in inpatient hospitalization or prolongation of existing hospitalization for ≥ 24 hours 4. A persistent or significant incapacity or substantial disruption of the ability to conduct normal life functions 5. A congenital anomaly/birth defect. 6. Important Medical Events (IME) that may not result in death, be life threatening, or require hospitalization may be considered serious when, based upon medical judgment, they may jeopardize the patient or subject and may require medical or surgical intervention to prevent one of the outcomes listed in this definition. (FDA, 21 CFR 312.32; ICH E2A and ICH E6). | | |
| --- | --- | --- |
| **ALL SERIOUS** adverse events that meet the above criteria MUST be immediately reported to the NCI via electronic submission within the timeframes detailed in the table below. | | |
| **Hospitalization** | **Grade 3-5**  **Timeframes** |  |
| Resulting in Hospitalization  ≥ 24 hrs | 24-Hour 5 Calendar Days |  |
| Not resulting in Hospitalization  ≥ 24 hrs |  |
| **NOTE:** Protocol specific exceptions to expedited reporting of serious adverse events are found in the Specific Protocol Exceptions to Expedited Reporting (SPEER) portion of the CAEPR.  **Expedited AE reporting timelines are defined as:**   - “24-Hour; 5 Calendar Days” – The AE must initially be submitted electronically within 24 hours of learning of the AE, followed by a complete expedited report within 5 calendar days of the initial 24-hour report. | | |
| 1Serious adverse events that occur more than 30 days after the last administration of investigational agent/intervention and have an attribution of possible, probable, or definite require reporting as follows:  **Expedited 24-hour notification followed by complete report within 5 calendar days for:**   - All Grade 3, 4, and Grade 5 Aes | | |

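### Sections 6.3 and 6.4 set conflicting scopes and clocks for SAE reporting, and non-serious DLTs at the second site have no prompt route to the lead site

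*Protocol*

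**What the plan says.** Section 6.3 (Expedited Adverse Event Reporting) tells investigators to report SAEs to the sponsor, named there as NCI, "whether or not they are considered related to the investigational agent(s)/intervention". On timing it says "The AE must initially be submitted electronically within 24 hours of learning of the AE", with the complete report due within 5 calendar days of that first one.

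Section 6.4 (AE Reporting) works differently. Drug-related SAEs "will be reported to all regulatory agencies by the study PI" within 7 working days. For the second site, "Any drug-related SAEs reported by a study participant at the University of Wisconsin will be reported to the JHU PI within 3 business days", and the reason given is "in order to allow sufficient time for the expedited reporting by the JHU PI". Expected adverse events at the second site are to be in REDCap within 2 weeks. No time is stated for unexpected events that are not serious.

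The rules that drive the trial use grade. The opening of Section 6 says "the stopping rule for safety is the presence of drug-related Grade 3 toxicity in any organ system". It also suspends accrual after two identical unexpected treatment-related toxicities of Grade 2 or more, or other toxicity of Grade 3 or more. Section 5.2 counts drug-related toxicity from Grade 2 as a DLT. None of these rules refers to seriousness.

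**The concern.** Two problems are joined here.

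First, a site reading Sections 6.3 and 6.4 gets two answers on which SAEs to report and how fast, and no rule of precedence. The second site is affected most, because Section 6.4 makes the lead-site PI the person who files the expedited report, yet allows 3 business days before that person is told.

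Second, the two sites share cohorts of three under one 3 + 3 scheme, in which a single event changes the next step. The inter-site clock is attached to drug-related SAEs, but the events that count are DLTs and drug-related Grade 3 toxicities. Many of these will not be serious. The lead site could go on enrolling and dosing at the current level for days without knowing of an event that counts toward the DLT total or triggers the stopping or suspension rule.

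**Working it through.** **1. The rules side by side.** There is no planned figure to reproduce.

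| | Section 6.3 | Section 6.4 |
|---|---|---|
| Which SAEs | any, regardless of attribution | drug-related only |
| Reported to | sponsor (NCI) | lead-site PI, then agencies |
| First clock | 24 hours from learning of the event | 3 business days, second site to lead-site PI |
| Later clock | complete report in 5 more calendar days | 7 working days, PI to agencies |
| Which governs | not stated | not stated |

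The definitions of a serious event also differ. Section 6.3 includes important medical events and a 24-hour hospitalization threshold. Section 6.1 has neither.

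**2. Business days in calendar days** (counted from each weekday, no public holidays).
- 3 business days: Monday, Tuesday or Sunday gives 3; Saturday gives 4; Wednesday, Thursday or Friday gives 5. Range 3 to 5.
- 7 working days: range 9 to 11.
- If the 7 days start only when the PI is told, 3 + 7 = 10 business days: range 12 to 14.
- Section 6.3, by comparison: 1 day for the first report and 1 + 5 = 6 days for the complete one.

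The shortest hand-off (3 days) is already longer than 1 day. If the lead-site PI files the expedited report and the clock starts when the site learns of the event, a hand-off that uses the allowed time misses the deadline whatever the weekday.

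**3. Events that count but are not SAEs.** Section 6.4 treats an event as unexpected only if it is not listed in sources that include the protocol. The synopsis lists dizziness, nausea, emesis and abdominal pain. A drug-related Grade 2 dizziness at the second site would therefore be an expected event, with 2 weeks for database entry, and also a DLT under Section 5.2. A Grade 2 or 3 event that is unexpected and not serious has no stated inter-site time.

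**4. What can happen in the interval.** Section 14.2 expects 6 evaluable patients per month. With 30.4 days per month, expected enrolments = 6 / 30.4 × days. Under a Poisson assumption, the chance of at least one = 1 − exp(−expected).

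| Days | Expected | Chance of at least one |
|---|---|---|
| 1 | 0.20 | 0.18 |
| 3 | 0.59 | 0.45 |
| 5 | 0.99 | 0.63 |
| 14 | 2.76 | 0.94 |

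The rate is for the whole trial, is not split by site, and ignores cohort caps. The figures are therefore on the high side for one site with a partly filled cohort.

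**5. Moves to the next dose level.** Section 14.1 has a 1-week washout before the next level, and Section 5.2 runs the DLT window to 1 week after the last cycle. A delay of 3 to 5 days is shorter than 7 days. It outlasts the wait only if those two weeks are the same week and the event falls late in it; the protocol does not say whether they coincide. The 14-day entry allowance is longer than the 7-day washout.

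**The case against.** The strongest reply is that the clocks have different recipients. A second-site investigator could file with NCI in 24 hours and tell the lead-site PI by day 3. The phrase about the PI's expedited reporting follows the 7-working-day sentence and may refer to that report; 3 days fit within 7. Section 6.3 also has limits of its own: its timeframe column is headed Grade 3-5, and it allows protocol-specific exceptions. This softens the conflict but does not remove it. The word expedited belongs to the Section 6.3 procedure, Section 6.4 appears to place that report with the lead-site PI, and the difference in scope remains under either reading.

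Several stronger readings are tempting, and the protocol does not support them.
- *Unrelated SAEs never reach the lead investigator.* They do: adverse events go on the CRF (6.3), both sites' data enter one REDCap database and the PI reviews all CRFs weekly (10.1), and the lead site compiles events from both institutions (6.4). What is missing is a prompt clock.
- *Central review of attribution is lost.* The weekly CRF review and the lead institution's monitoring committee (Section 12) remain.
- *The 7 working days keep the escalation in the dark.* By then the PI already knows.
- *The drug-related filter hides stopping events.* The stopping rule is itself limited to drug-related toxicity. The filter matters only if relatedness is judged late or differently between sites.
- *A patient elsewhere would typically finish a whole cycle in the interval.* That needs a weekend, full use of the 3 days, and a first dose just as the event becomes known. Compared with a 24-hour clock, the excess is 2 to 4 days, less than the 5 daily doses of a cycle.

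**Conclusion.** The concern holds as a conflict in protocol text. Sections 6.3 and 6.4 differ on scope and clock, and neither takes precedence. A second-site hand-off of 3 to 5 calendar days cannot serve a 24-hour deadline, given the natural reading that the lead-site PI files the expedited report and the clock starts when the site learns of the event.

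For the escalation, the more important gap is that DLTs and stopping events are set by grade, and non-serious ones at the second site have no prompt inter-site clock. The supported consequence is continued enrolment and dosing at the current level: about 0.6 to 1.0 expected enrolments over 3 to 5 days and about 2.8 over 2 weeks, against 0.2 over one day. These rest on the stated accrual rate, full use of each allowance and no cohort caps. A reader might infer that the trial would move to a higher dose unaware of an event. The DLT window, the washout and the weekly CRF review partly protect against that, and the protocol does not say who makes the escalation decision.

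**What to change.** - Reconcile Sections 6.3 and 6.4 on four items: which SAEs are covered (with one SAE definition shared with Section 6.1), when the clock starts, who receives each report, and who submits the expedited report.
- Replace the 3-business-day notification with the 24-hour clock already in Section 6.3. Apply it to any SAE at the second site regardless of attribution, and to any event that could count as a DLT under Section 5.2 or meet the stopping or suspension rule in Section 6.
- Name the agencies to which the 7 working days apply, so that this text does not override the 24-hour and 5-day table. It need not be deleted.

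The cost is protocol wording, a reminder to the sites and slightly faster reporting work at the second site. Sample size and analysis are unaffected.

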## Description of Study Medication

## Study Medication: Suppository Formulation of Artesunate

## Drug Substance

Artesunate is a derivative of artemisinin, which is the active principle of the Chinese medicinal herb *Artemisia annua*.

Nomenclature Artesunate, Artesunic acid

Chemical Name [3*R*, 5a*S*,6*R*,8a*S*,9*R*,10*S*,12*R*,12a*R*)-3,6,9-

trimethyldecahydro-3,12-epoxypyrano[4,3-*j*]-1,2- benzodioxepin-10-ol, hydrogen succinate;

CAS Reg. No. 88495-63-0

[figure not shown]

General Properties

Molecular Formula C19H28O8

Molecular Weight 384.4 g/mol

Physical Description A fine, white crystalline powder

Solubility Very slightly in water; very soluble in dichloromethane; freely soluble in ethanol (~ 750 g/l) and acetone

Melting Point 132-135ºC

Optical Rotation R; [α] D 20 °C = +2.5° to +3.5° in a 10mg/mL in

dichloromethane

pH 3.5-4.5 in an aqueous suspension containing 10 mg/g

## Suppository Formulation

Artesunate suppositories will be produced under controlled environmental conditions as prescribed in USP Chapter 795. Artesunate will be added and dissolved into a molten fatty acid base. The mixture will then be transferred into disposable pre-formed suppository molds to cool into solid suppositories.

Clinical trial supplies will be produced by Buderer Drug Co. in Perrysburg, Ohio. Buderer maintains compliance with USP Chapter 795 (Pharmaceutical Compounding – Nonsterile Preparations) and USP Chapter 797 (Pharmaceutical Compounding – Sterile Preparations), which establish practice standards and outline the responsibility of the compounder, selection and appropriate sources of ingredients, quality control, and considerations regarding the stability of compounded preparations. Two additional USP informational chapters are in effect, including, USP Chapter 1075 – Good Compounding Practices, and USP Chapter 1160 – Pharmaceutical Calculations in Prescription Compounding.

## Packaging and Labeling

Suppositories for dispensing will be packaged in standard prescription use plastic or cardboard containers. Proper labeling will be applied per state regulations.

## Product Storage and Stability

The suppositories may be stored at controlled room temperature. Suppositories for dispensing will be packaged in plastic or cardboard container, and kept in their plastic mold until administration.

USP 795 designates a beyond use date for this preparation not longer than 6 months. Potency testing will be obtained to validate the preparation process.

## Dosage and Administration

the first dosing visit (week 0) will be an in-person visit, in which tthe study physician or nurse will administer the first of five daily intra-anal suppositories for each enrolled subject at the study site. The subjects will be trained by the physician or nurse on the insertion of artesunate suppositories transanally during that visit, and instructed to administer four subsequent daily doses at home. All subsequent dosing visits (weeks 2 and 4) will be performed as telemedicine visits. For telemedicine visits, the physicians will review the symptom diaries and patients will be instructed about suppository administration over the phone. Within 5 days of the last day of the cycle(s), patients will receive a telephone call to assess for any AE. If patients do not experience any symptoms or AEs after suppository administration, then the subsequent dosing visits will be telemedicine visits. However, if patients experience AEs, then the subsequent dosing visits will be in-person visits, at which time the physician will perform an anoscopy.

The first 3 study subjects (healthy volunteers with AIN2/3) will receive five (5) daily suppositories that contain 200 mg Artesunate for a total of 2 cycles at weeks 0 and 2. The 200 mg dose (or ≤ 4 mg/kg for subjects weighing 50 kg at minimum) is considerably lower than that used when the anal suppository is intended to deliver a systemic dose of drug for malaria – the 10 mg/kg (50 mg) suppository is recommended by WHO for pediatric care. If no severe local irritation or systemic toxicities are observed in the first 3 patients at 200 mg, the dosage will escalate to 3 cycles of 200 mg per day. Doses of escalation will be 200 mg, 400 mg, and 600 mg. Suppositories will be administered daily for 5 days. Five days constitutes 1 cycle. Up to 3 cycles will be administered at Weeks 0, 2, and 4. Please see section 5 for dose escalation schema.

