| **Concept and Rationale:**  Up to 95% of anal cancers (anal squamous cell cancers, ASCC) are caused by human papillomavirus (HPV)[1](#_ENREF_1); however, current management of pre-cancerous lesions (anal intraepithelial neoplasia, AIN) consists of surgical excision or ablation and this does not treat the underlying cause of HPV infection. Recurrences are common; in HIV-seronegative persons treated with ablation, recurrence is as high as 50% within one year [2](#_ENREF_2). The morbidity of these destructive ablations is significant and includes anal stenosis and fecal incontinence.  Artesunate, formulated as a suppository, is WHO-approved for first-line treatment for acute malaria in children who are located in remote settings with limited access to healthcare [3](#_ENREF_3). Globally, Artesunate has been administered to 2 million people [4](#_ENREF_4), given orally, intramuscularly, intravenously, and as rectal suppositories, providing a wealth of safety information. Both Artesunate and dihydroartemisinin, an Artesunate metabolite, have been shown to be cytotoxic to epithelial cells expressing HPV16 E6 and/or E7, while having no effect on uninfected cells [5](#_ENREF_5). Both ASCC and AIN2/3 (high-grade anal intraepithelial neoplasia) are associated with functionally obligate expression of two viral proteins, E6 and E7. Epithelial cells that express either or both of these oncoproteins overexpress the transferrin receptor, and have increased levels of intracellular iron, compared to normal cells [6](#_ENREF_6). Artesunate contains an endoperoxide bridge that reacts with intracellular ferrous iron to generate free radicals, leading to cell death .  This observation raises the possibility of treating pre-invasive HPV disease (i.e., AIN2/3) with an effective anti-malarial drug, Artesunate, administered as an intra-anal suppository. The toxicity profile of this formulation is well-documented and includes dizziness, nausea, emesis, and abdominal pain. It should be noted that these symptoms are also commonly experienced in active malarial infection. Preliminary data from an ongoing study of intravaginal administration of Artesunate suppositories for cervical dysplasia has demonstrated mucosal irritation as the only adverse event.  This study investigates a novel non-surgical approach to the treatment of HPV-associated anal intraepithelial neoplasia, using topical Artesunate. |

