## Definition of Dose-Limiting Toxicity

A dose-limiting toxicity (DLT) is defined as any drug-related Grade 2 (moderate; minimal, local, or noninvasive intervention indicated; limiting age appropriate instrumental ADL) or greater drug-related toxicities in any organ system (or Grade 3 or greater toxicities–severe or medically significant but not immediately life-threatening; hospitalization or prolongation of hospitalization indicated; disabling; limiting self care ADL**) in any organ system (including gastrointestinal, dermatologic, and neurologic), as delineated in Common Terminology Criteria for Adverse Events v4.0 (CTCAE).

This above definition of dose-limiting toxicity applies to the drug that is being studied—the artesunate suppository. Post-procedural complications related to the HRA procedure are not dose limiting.

The dose limiting toxicity determining period for the study will extend to 1 week after the last cycle of artesunate suppository. Thus, for the 2 cycles, the DLT determining period will extend to 3 weeks; for 3 cycles, it will extend to 5 weeks.

Beyond the DLT determining period, if patients in a specific cohort have complete resolution of their high-grade dysplastic lesions, then the plan will be to stop at this dosing cycle and frequency and move into the 12-patient expansion cohort.

Management and dose modifications associated with the above adverse events are outlined in Section 6.

Dose escalation will proceed within each cohort according to the modified 3+ 3 design with de-escalation schema and an expansion cohort at MTD. Dose-limiting toxicity (DLT) is defined as above.

The specific details are as follows,

The 3 + 3 dose escalation will consist of 6 dose levels in combination with variation in dosing schedules the single agent Artesunate, with additional de-escalation steps. An expansion cohort of 12 patients will be included at the MTD. Once MTD is found, then secondary outcomes will be evaluated. In MTD expanded patient cohort, anal intraepithelial neoplasia (AIN) regression from AIN 2/3 to low-grade anal intraepithelial neoplasia (AIN 1) or no residual AIN will be assessed through subsequent HRA evaluation. Cytology specimens will be tested through quantitative PCR for HPV viral load during initial and subsequent HRA evaluations. A tissue bank will be created for future studies.

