# STATISTICAL CONSIDERATIONS

## Study Design/Endpoints

The primary objective of this trial is to determine the MTD or recommended Phase 2 dose (RP2D) of Artesunate. The MTD will be determined using a modified 3 + 3 design, in which the MTD is defined as the highest dose level tested at which ≤20% patients experience dose limiting toxicity (DLT). The 3 + 3 dose escalation will consist of 6 dose levels in combination with variation in dosing schedules the single agent Artesunate. In addition, if DLT’s are identified at any dose, there are possible intermediate dose de-escalation steps allowed (i.e. to have only one administration at a particular dose) An expansion cohort will occur at MTD. Once MTD is found, then secondary outcomes will be evaluated. There is a 1-week washout period before advancing to the next Artesunate dose level.

| **Dose Escalation Design** | | | | |
| --- | --- | --- | --- | --- |
| **Cohort** | **Dose (mg)** | **Number of Treatment Cycles** | **Designated Weeks of Artesunate Administration** | **Number of patients** |
| **I** | 200 | 2 | 0, 2 | 3 |
| **II** | 200 | 3 | 0, 2, 4 | 3 |
| **III** | 400 | 2 | 0, 2 | 3 |
| **IV** | 400 | 3 | 0, 2, 4 | 3 |
| **V** | 600 | 2 | 0, 2 | 3 |
| **VI** | 600 | 3 | 0, 2, 4 | 3 |

More specifically:

This is a modified 3 + 3 design. Based on previous studies of rectally administered Artesunate for the treatment of malaria, the safety profile demonstrates a low probability of dose limiting toxicity in children, as well as adults. The first cohort will consist of 3 patients who receive the initial dose of a 200-mg suppository administered in cycles of 5 daily doses at weeks 0 and 2. If none of the three patients in a cohort experiences a dose-limiting toxicity, another three patients will be treated at the next higher dose level. If 1 out of 3 patients experiences dose-limiting toxicity, then the next 3 patients will be treated at the same dose level. If 2 out of 6 patients experience a DLT, then de-escalation to the next lower level will occur. The modification of the 3 + 3 design consists of the extra de-escalation steps as noted on the left of the diagram pictured below.

If any dose has 2 (or more) DLTs then the MTD will be the dose that is below that dose that has 1 or less DLTs out of 6 patients. Once the MTD is identified then additional patients will be added to this cohort to allow a total of 12 patients.

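### Section 6.9 lets cohort I escalate past Grade 2 local irritation, which Sections 5.1 and 5.2 count as a DLT and which blocks escalation under Section 14.1

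*Protocol*

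**What the plan says.** **Section 6.9, Dosage and Administration.** The move from cohort I to cohort II has its own criterion: "If no severe local irritation or systemic toxicities are observed in the first 3 patients at 200 mg, the dosage will escalate" to three cycles at the same 200 mg dose. The paragraph closes with "Please see section 5 for dose escalation schema".

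**Section 5.2, Definition of Dose-Limiting Toxicity.** "A dose-limiting toxicity (DLT) is defined as any drug-related Grade 2 (moderate; minimal, local, or noninvasive intervention indicated" and so on, or greater, in any organ system. A parenthesis then adds Grade 3 or greater, which it describes as "severe or medically significant but not immediately life-threatening". Section 5.1 sets the same Grade 2 threshold with a similar parenthesis.

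**Section 14.1, Study Design/Endpoints.** The rule works on DLT counts:
- 0 of 3: "If none of the three patients in a cohort experiences a dose-limiting toxicity, another three patients will be treated" at the next level.
- 1 of 3: "If 1 out of 3 patients experiences dose-limiting toxicity, then the next 3 patients will be treated at the same dose level".
- Two or more DLTs at a level: the level fails, and "the MTD will be the dose that is below that dose that has 1 or less DLTs out of 6 patients".

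**Protocol Synopsis, Concept and Rationale.** The ongoing intravaginal study of artesunate suppositories "has demonstrated mucosal irritation as the only adverse event". No grade is given.

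**The concern.** Section 6.9 and Section 14.1 both say when cohort I may escalate, and they use different thresholds. A moderate local reaction passes the Section 6.9 test but is a DLT under Section 5.2, so it holds or fails the level under Section 14.1.

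The MTD is the primary endpoint, and this is the first escalation decision, on which every higher level depends. If Section 6.9 were followed after one Grade 2 local reaction, the three further patients that Section 14.1 requires at cohort I would not be treated before the next patients received a third cycle. After two or three such reactions the instructions point in opposite directions: Section 6.9 adds a cycle, while Section 14.1 moves down, and the only lower step in the schema is 200 mg for one cycle.

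**Working it through.** **1. The two rules side by side.** Take the first three patients in cohort I, with drug-related Grade 2 local irritation as the only toxicity seen.

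| Patients with Grade 2 local irritation | Section 6.9 | Sections 5.2 and 14.1 |
|---|---|---|
| 0 of 3 | escalate | escalate |
| 1 of 3 | escalate | treat 3 more at the same level |
| 2 or 3 of 3 | escalate | level fails, de-escalate |

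The rules agree only in the first row.

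**2. Inputs.** The cohort size of 3 and the counts come from Section 14.1. The DLT threshold comes from Section 5.2. The protocol states no rate of Grade 2 local irritation and no operating characteristic for this decision, so there is no figure of the plan's own to reproduce. The rate *p* is assumed at 5%, 10% and 20%, with patients independent and no other DLT. Section 14.1 does not say in words that 1 of 6 permits escalation. It is taken to, because a level with at most 1 DLT in 6 qualifies as the MTD.

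**3. Chance that the rules differ after three patients.** This is the chance of at least one Grade 2 local DLT: 1 − (1 − p)³.
- p = 0.05: 1 − 0.857 = 0.143
- p = 0.10: 1 − 0.729 = 0.271
- p = 0.20: 1 − 0.512 = 0.488

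**4. Chance that the full Section 14.1 rule fails cohort I.** The level passes at 0 of 3, or at 1 of 3 followed by 0 of 3. Failure is 1 − [(1 − p)³ + 3p(1 − p)² × (1 − p)³].
- p = 0.05: 1 − (0.857 + 0.135 × 0.857) = 1 − 0.973 = 0.027
- p = 0.10: 1 − (0.729 + 0.243 × 0.729) = 1 − 0.906 = 0.094
- p = 0.20: 1 − (0.512 + 0.384 × 0.512) = 1 − 0.709 = 0.291

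Under the same assumptions Section 6.9 never fails the level, because no severe event occurs.

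**5. Chance of directly opposite instructions after three patients.** This needs at least two Grade 2 local DLTs: 3p²(1 − p) + p³.
- p = 0.05: 0.0071 + 0.0001 = 0.007
- p = 0.10: 0.027 + 0.001 = 0.028
- p = 0.20: 0.096 + 0.008 = 0.104

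**The case against.** **Section 6.9 is narrative, and Section 14.1 governs.** The sentence sits under pharmaceutical information, covers only the first three patients, and sends the reader to Section 5. Someone who reads the whole protocol could work out that the 3 + 3 counts are meant. This limits the reach of the problem but does not remove it. The sentence is a complete, operative criterion, no clause gives another section precedence, and following the reference leads to Section 5.2, which contradicts it.

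**The DLT threshold is itself blurred.** Sections 5.1 and 5.2 name Grade 2 or greater and then add Grade 3 or greater in parentheses. If Grade 3 were the working threshold, Section 6.9 would agree on local irritation. But Grade 2 is named first and without qualification, and Section 14.3 treats a toxicity as an event at least possibly related to treatment, so a Grade 3 toxicity is already included in Grade 2 or greater. The parenthesis adds nothing, but it does confuse and belongs in the fix. Section 6.9 also cites no CTCAE grade; equating its severe with Grade 3 is an inference from Section 5.2, though the natural one.

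**The chances rest on assumed rates, and many of the differing cases would end in escalation anyway.** Both points stand. Of the cases where the rules differ, those that would still advance under Section 14.1 after three more patients are about 81% at p = 0.05 (0.116 of 0.143), 65% at 0.10 (0.177 of 0.271) and 40% at 0.20 (0.197 of 0.488).

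**Two stronger readings that the protocol does not support.**
- A reader might infer that the two sites could escalate differently after the same event. Section 10.1 describes one shared database, weekly review of case report forms by the principal investigator, and an initial toxicity review after the first treatment group. Escalation is one central decision; the difficulty is that this decision has two written criteria.
- A reader might infer that the Grade 3 stopping rule in Section 6 also contradicts Section 14.1. It would do so only if it ended the trial, which no text says. The next sentence of Section 6 suspends accrual pending review, a response that covers Grade 3 or greater, and a pause followed by the Section 14.1 counts is coherent. That is at most a wording clarification.

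**Conclusion.** The contradiction is real and lies in the protocol's own terms: Section 6.9 lets cohort I escalate past Grade 2 local irritation that Sections 5.1 and 5.2 make a DLT and Section 14.1 does not allow to pass at once. It is limited to the cohort I to cohort II step, which adds one cycle at the same dose, and to local irritation. Whether severe also qualifies the systemic toxicities in that sentence is unclear, so nothing is claimed about them. Cohort II and later levels would still be judged under Section 14.1.

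On assumed Grade 2 local rates of 5% to 20% with no other DLT, the rules differ after three patients with chance 14% to 49%, and Section 14.1 would fail cohort I with chance 2.7% to 29%. The contradiction does not depend on these rates; only its size does. It should be corrected because it governs patients' exposure and the primary endpoint, and correction costs almost nothing.

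**What to change.** 1. In Section 6.9, replace the cohort I criterion with a statement that escalation follows the DLT definition in Section 5.2 and the counts in Section 14.1.
2. In Sections 5.1 and 5.2, delete the parenthesis on Grade 3 or greater toxicities, so that any drug-related Grade 2 or greater toxicity is plainly the threshold. Without this, the new reference in Section 6.9 would lead to a blurred definition.
3. Optionally, clarify in Section 6 that a drug-related Grade 3 event suspends accrual pending review, after which the Section 14.1 counts apply.

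The cost is a wording amendment. It adds no procedures and leaves the planned 36 patients (6 levels × 6) and the maximum of 60 unchanged.
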